## Abstract

**Background:**

Catheter-related bladder discomfort (CRBD) is common in male patients under general anesthesia, and it may cause patient agitation and exacerbated postoperative pain. In this study, we will enroll male patients undergoing elective surgery with urinary catheterization after anesthetic induction and compare the efficacy of a dorsal penile nerve block (DPNB) and intravenous tramadol for the prevention of CRBD.

**Methods/Design:**

This trial is a prospective, open-label, randomized controlled trial that will test the superiority of a dorsal penile nerve block with 0.33 % ropivacaine to the use of intravenous tramadol 1.5 mg/kg for CRBD prevention. A total of 60 male patients undergoing elective surgery with urinary catheterization after anesthetic induction will be randomized to receive either DPNB with 0.33 % ropivacaine (DPNB group) or intravenous tramadol 1.5 mg/kg (TRAM group) after the completion of surgery but before extubation. The primary outcome is the incidence and severity of CRBD. Secondary outcomes include Visual Analog Score (VAS) for postoperative pain, number of patients requiring sulfentanil after operation, acceptance of an indwelling urinary catheter after extraction of the catheter, and postoperative side effects, which include postoperative nausea/vomiting (PONV), vertigo, sedation, drowsiness, and dry mouth.

**Discussion:**

For CRBD prevention, this trial is planned to test the superiority of a dorsal penile nerve block with 0.33 % ropivacaine to the use of intravenous tramadol 1.5 mg/kg. The results will provide new insight into the mechanism of CRBD and new clinical practice for the prevention of CRBD.

**Trial registration:**

The registration number is NCT01721031, which was assigned by the National Institutes of Health Clinical Trials Registry (ClinicalTrials.gov) on 27 October 27.

## Background

Catheter-related bladder discomfort (CRBD) due to an indwelling urinary catheter includes a distressing complex of symptoms such as an urge to void, irritation of the urethra, and discomfort in the supra-pubic region [1]. The incidence of CRBD ranges from 47 to 90 % in the postoperative period, especially in male patients who have had urinary catheterization after anesthetic induction under general anesthesia [1–4]. CRBD often causes patient agitation and is accompanied by behavioral responses that may include loud complaining and attempts to remove the urinary catheter. In addition, CRBD may result in exacerbated postoperative pain, increased postoperative complications, and prolonged hospital stay. Therefore, it is necessary to prevent and treat CRBD as early as possible.

The mechanism of CRBD has been reported to be similar to that of overactive bladder, that is, the involuntary contraction of the detrusor muscles of the urinary bladder, which is caused by acetylcholine released from activated cholinergic nerves and mediated by muscarinic receptors [1]. Therefore, muscarinic receptor antagonists such as tolterodine, oxybutynin, ketamine, butylscopolamine, and tramadol have been reported to be effective in the prevention or treatment of CRBD with a variable successful rate [5–9]. However, side effects such as sedation, nausea or vomiting, dry mouth, or other unpleasant complications may occur with these systemic administrations. Clinically, the dorsal penile nerve block (DPNB) has been applied in penile surgery for decades, and satisfactory pain relief effect could be achieved during operation and postoperatively without the side effects related to systemic administrations [10–13]. In addition, we have observed that patients undergoing urethral surgery with a urinary catheter left in-situ seldom complained about CRBD if the DPNB is performed at the end of operation. Based on these literatures and clinical practice, we hypothesize that DPNB could relieve CRBD for male patient with an indwelling urinary catheter if the insertion occurs after the induction of general anesthesia.

In this trial, we will compare the efficacy of a dorsal penile nerve block with 0.33 % ropivacaine to intravenous tramadol 1.5 mg/kg in the prevention of CRBD, as well as the incidences of postoperative side effects. To the best of our knowledge, this is the first trial that examines the use of the nerve block technique for CRBD prevention.

## Methods/Design

### Design

The DPNB trial is a prospective, open-label, randomized controlled trial that will test the superiority of a dorsal penile nerve block with 0.33 % ropivacaine to intravenous tramadol 1.5 mg/kg for CRBD prevention. The protocol of the trial has been registered at http://www.clinicaltrials.gov/NCT01721031 (NCT01721031), and a brief flowchart of the whole study is summarized in Fig. 1.

**Fig. 1 Fig1:**
[figure not shown]
The dorsal penile nerve block (DPNB) trial flowchart

This trial is investigator initiated without any external financial sponsorship, and no company has played any role in the development, implementation, or data collection and analysis of this study. The authors and their colleagues are responsible for the trial design and execution; related statistical analysis; and all aspects of the manuscript preparation, including drafting, editing, and decisions on the final content. This study will be conducted according to the principles outlined in the Declaration of Helsinki. All investigators are appropriately qualified by training to conduct the trial. All patients have to sign the informed consent prior to study entry.

### Ethics

This study protocol has been approved by the Biological-Medical Ethical Committee of West China Hospital, Sichuan University, Chengdu, Sichuan, China, on 10 October 2012. Details of the study will be explained thoroughly to the potential subjects and/or his legal guardian by the investigator, and the signed informed consent form must be provided by all eligible patients before their participation in the study. Patients will be given at least 24 hours to decide whether they want to participate in the study. Participation in the study is entirely voluntary, and patients can withdraw from the study at any time. The privacy of all participants will be protected. Personal medical records will be checked by investigators and inspectors, and they will not export any confidential information. Data anonymity is ensured in the whole process of data management, and the data of all subjects will be kept within the Department of Anesthesiology, West China Hospital of Sichuan University.

### Recruitment

A total of 60 patients undergoing elective general surgery or orthopedic surgery with urinary catheterization (18 G Fr Foley catheter) after anesthetic induction under general anesthesia will be enrolled at two hospitals in China: the West China Hospital of Sichuan University and the First People’s Hospital of Neijang.

### Randomization and blinding

All patients recruited to the study will be collectively randomized using Statistical Analysis System (SAS 9.1) by the Department of Anesthesia, West China Hospital of Sichuan University. The responsible anesthesiologist will call the research nurse to get the randomization number and the allocated group. The investigators, responsible anesthesiologists, surgeons, and the research nurse will be aware of the treatment allocation. The patients, staff responsible for follow-up, and statisticians will be blind to the treatment assignment.

### Entry criteria

#### Inclusion criteria

The inclusion criteria are as follows:Male patients aged 18 years to 50 years.American Society of Anesthesiologists (ASA) physical status I, II, or III.Undergoing elective general liver surgery and orthopedic extremity surgery with urinary catheterization after anesthetic induction under general anesthesia.Glasgow Coma Scale (GCS) score of 15.Ability to communicate.

#### Exclusion criteria

The exclusion criteria include the following:Refusal to sign consent.History of bladder dysfunction, such as overactive bladder (OAB, urinary frequency is more than three times in the night or more than eight times in 24 h).Psychopathy.Impaired renal function.History of bladder outflow obstruction.Neurogenic bladder.Prostate disease.Known allergies to any anesthetic agent.Family history of malignant hyperthermia.Coagulopathy.Impairment of communication or cognition.Active participation in another trial where the primary endpoint follow-up is ongoing.Unwillingness or inability to comply with protocol procedures.

### Interventions

Patients in the DPNB group will be given a dorsal penile nerve block with 15 ml of 0.33 % ropivacaine after the completion of the surgery before extubation.

Patients in the TRAM group will be given tramadol of 1.5 mg/kg after the completion of surgery but before extubation.

### Outcome measures

All patients will be evaluated for outcomes at 0, 1, 2, 4, and 6 h after patients’ arrival in the post-anesthesia care unit (PACU) and after extraction of urinary catheter.

#### Primary outcome

The primary outcome is the incidence and severity of CRBD, which will be assessed according to the following scaling system: no CRBD indicates that there are no complaints of CRBD at all; mild indicates that complaints of CRBD exist only if the patient was asked about it; moderate indicates that patients complain of CRBD spontaneously; and severe indicates that the CRBD causes a spontaneous behavioral response such as flailing limb, strong vocal response, or attempt to pull out the catheter [2].

#### Secondary outcomes

The secondary outcomes include the following:2.7.2.1.Visual Analogue Score (VAS) for postoperative pain.2.7.2.2.Number of patients requiring postoperative sulfentanil.2.7.2.3.Postoperative sufentanil requirement.2.7.2.4.Duration of postoperative sulfentanil requirement.2.7.2.5.Postoperative side effects, which include the following: (1) postoperative nausea/vomiting (PONV), (2) vertigo, (3) sedation, (4) drowsiness, and (5) dry mouth.2.7.2.6.Acceptance of an indwelling urinary catheter after extraction of the catheter.

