## Discussion

Tramadol is a weak opioid that is commonly used for postoperative pain relief [14, 15], and it is reported to halve the incidence of CRBD if it is administered i.v. 30 min before the end of surgery [9]. Therefore, we chose tramadol treatment as the control and are testing the superiority of a dorsal penile nerve block with 0.33 % ropivacaine over the intravenous tramadol 1.5 mg/kg in CRBD prevention.

Dorsal penile nerve block, a local anesthetic technique, has been applied widely in patients undergoing urethra surgery, and these patients, with a urinary catheter left in situ, rarely complain about CRBD. Theoretically, the nerve block should be associated with fewer side effects when compared with intravenous administration. Therefore, we hypothesize that DPNB could reduce the incidence of CRBD as well as the side effects. In addition, the afferent nerves of the urethra and bladder triangle are derived from sacral somatic (S2 to 4) [16], and a successful prevention of CRBD could be achieved by blocking the pudendal nerve. If the prevention of the CRBD can be achieved by the DPNB, a new mechanism of CRBD other than overactive bladder would be suggested by this trial.

In terms of the study design, the diameter of the 18 G Fr Foley catheter and the sex (male) has been reported to be independent predictors of moderate or severe CRBD in the PACU [1], so we choose male patients with 18 G Fr Foley catheter to test the effects of CRBD prevention in the current study. In addition, the local anesthetics are not applied for catheterization to minimize other factors related to CRBD. Furthermore, although we test the superiority of the dorsal penile nerve block with 0.33 % ropivacaine to intravenous tramadol 1.5 mg/kg in CRBD prevention, we are not going to cast doubt on the beneficial effects of anti-cholinergic drugs to relieve CRBD.

The limitation of this trial is that DPNB is only applicable to surgical patients undergoing general anesthesia. The application of DPNB should be studied in the future to benefit those patients who are undergoing catheterization for medical procedures not requiring any surgical intervention.

In conclusion, this trial plans to test the superiority of a dorsal penile nerve block with 0.33 % ropivacaine to intravenous tramadol 1.5 mg/kg in CRBD prevention. This study may provide a new insight into the mechanism of CRBD and new clinical practice for the prevention of CRBD.

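### The side-effect list contains nothing specific to the nerve block, so it cannot support the hypothesis that DPNB reduces side effects in general

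*Protocol article*

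**What the plan says.** Secondary outcomes (item 2.7.2.5) gives the side-effect outcome as "Postoperative side effects, which include the following: (1) postoperative nausea/vomiting (PONV), (2) vertigo, (3) sedation, (4) drowsiness, and (5) dry mouth". The Abstract repeats the same five: "postoperative side effects, which include postoperative nausea/vomiting (PONV), vertigo, sedation, drowsiness, and dry mouth".

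The Background says where it expects such effects to come from: "side effects such as sedation, nausea or vomiting, dry mouth, or other unpleasant complications may occur with these systemic administrations". Of the block it says that "satisfactory pain relief effect could be achieved during operation and postoperatively without the side effects related to systemic administrations". It also names the incidence of side effects as something the trial will compare.

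The Discussion gives the reasoning, "Theoretically, the nerve block should be associated with fewer side effects when compared with intravenous administration", and then the hypothesis: "we hypothesize that DPNB could reduce the incidence of CRBD as well as the side effects". The Statistical analysis section compares side effects between groups by chi-square, with P < 0.05 as the criterion.

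Under Interventions, only the DPNB arm receives the penile injection (15 ml of 0.33% ropivacaine). No section of the article names a harm of that injection as an outcome.

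**The concern.** The hypothesis is general, but the measure mainly covers the harms expected of one arm. An effect typical of a systemic drug can count against tramadol. A harm arising only from the injection has no place in the list and cannot count against DPNB. If the trial then reports significantly fewer side effects with DPNB, readers may take this as a statement about overall tolerability. The data would support only a statement about five named symptoms.

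This matters because tolerability is part of the argument for the block. The Background and Discussion present it as a way to avoid the side effects of systemic treatment, and the block is an invasive procedure. Anyone weighing it against an intravenous drug needs the harms of both.

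**Working it through.** The plan gives no figure for side effects, so there is none to reproduce. The check compares the list with the text and then sizes what 30 patients could show.

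**1. The list against the document's own attribution**

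| Item in 2.7.2.5 | Attributed to systemic drugs in the Background? | Specific to the block? |
|---|---|---|
| PONV | Yes | No |
| Vertigo | Not named | No |
| Sedation | Yes | No |
| Drowsiness | Not named, though close to sedation | No |
| Dry mouth | Yes | No |

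Three of five are attributed to systemic drugs, and none of five is specific to the block.

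**2. Can the listed effects occur in the DPNB arm?** Yes. All patients have general anaesthesia, and postoperative sufentanil use is an outcome in both arms. DPNB patients can therefore have nausea, sedation or dry mouth, and would have more of them if they needed more sufentanil. The list is tilted, but it does not fix the result.

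**3. What could 30 DPNB patients show about block harms, if these were recorded?** The Sample size calculation gives 30 per group with 20% dropout.

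- Zero events in n patients gives a one-sided 95% upper bound of 1 − 0.05^(1/n).
- n = 30: 1 − 0.05^(1/30) = 0.095, or 9.5%.
- n = 30 × 0.80 = 24: 1 − 0.05^(1/24) = 0.117, or 11.7%.
- The chance of at least one event in 30 is 1 − (1 − p)^30. At an assumed true rate of 5% it is 79%, and at 10% it is 96%.

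Recording would probably reveal a common harm but could not rule out an uncommon one.

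**4. Could the choice of list change the conclusion?** This is an illustration only, because the document gives no rates and does not say whether the effects are tested singly or as any event. Assume an any-event comparison, two-sided 5%, 30 per arm, listed effects in 40% (TRAM) and 10% (DPNB), and independent block harms at rate b in the DPNB arm. The DPNB any-event rate is then 1 − 0.90 × (1 − b).

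| Assumed b | DPNB any-event rate | Power to show fewer events with DPNB |
|---|---|---|
| Not counted | 10% | 78% |
| 10% | 19% | 43% |
| 20% | 28% | 16% |
| 30% | 37% | 4% |

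Under these assumptions the list alone can decide whether the trial reports fewer side effects. The rates are not a forecast for this trial.

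**The case against.** The best case for the plan has four parts.

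- **The list may be open and the article is a condensation.** The wording says the side effects include these five, and a fuller protocol may provide for recording other adverse events. This stands in part: a reader might infer that no harm of the block will be recorded at all, and the article does not show that. But the items are numbered, the Abstract repeats the same five, and general adverse-event recording elsewhere would not place block harms in the outcome that is tested.
- **The hypothesis may be meant narrowly.** Read with the Background, the question may be only whether the block avoids the effects of systemic drugs, which the five items suit. If so, only the wording is at fault, but the Discussion sentence carries no such limit. It is also a hypothesis and not a planned conclusion: the article's closing statements concern CRBD prevention and its mechanism.
- **The effects can arise in either arm.** This stands. A reader might infer that a DPNB advantage is built into the measure, and the documents support only a tilt.
- **Looking for block harms could unblind.** This stands. Patients and follow-up staff are meant to be blind, and CRBD is partly a subjective rating. Inspecting the injection site or asking about numbness could reveal the allocation.

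Two further inferences fail. Listing both sedation and drowsiness does not count a patient twice, because no summed score is planned. Excluding coagulopathy and anaesthetic allergy does not show that the sponsor had block harms in mind: those criteria may equally reflect general anaesthesia or the liver surgery that is enrolled.

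**Conclusion.** The concern holds in a limited form. The side-effect outcome has no block-specific item, while the hypothesis attached to it is unrestricted and side effects are formally compared. The comparison therefore leans towards DPNB and cannot support a general claim of fewer side effects, though it can support a claim about the five listed effects.

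This rests on the article's own outcome list and hypothesis, not on anything left to a document that is not shown. The 9.5% bound assumes that all 30 DPNB patients are assessed and none has an event; with 24 assessed it is 11.7%. The power figures rest wholly on assumed rates and show only that the choice of list can matter. This is a secondary outcome, and the primary CRBD comparison is unaffected.

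**What to change.** 1. Add to outcome 2.7.2.5 a short prespecified set of block-related harms, for example injection-site bleeding or haematoma, penile numbness, signs of a local-anaesthetic reaction, and difficulty voiding after catheter removal. Record them in both arms at the assessments already planned, including the one after catheter removal, and report them beside the systemic effects.
2. Protect blinding: record these items after the CRBD rating at each assessment, or have them recorded by staff who already know the allocation.
3. Whether or not items are added, word the hypothesis and any conclusion as fewer of the listed systemic effects.
4. State with the results that zero block harms in 30 patients would exclude only rates above about 9.5% (one-sided 95%).

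The cost is a few extra items at existing assessments, some care over who asks and when, and a comparison that may look less favourable to DPNB. Step 3 alone costs nothing and is the minimum. Allowing a claim only on a combined any-event count would be a matter of preference and is not needed.

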### Quality control

The principal investigator, study coordinator, and Office of Scientific Research at West China Hospital are jointly responsible for all aspects of the study protocol and amendments. [name], Associate Professor in the Department of Anesthesiology, West China Hospital, will be responsible for site monitoring. Data collection and follow-up will be performed by two dedicated affiliated research nurses. Designated trial monitors will periodically review all investigational data for accuracy and completeness to ensure protocol compliance.

### Sample size calculation

A difference of 30 % in the incidence of CRBD values between the DPNB group and the TRAM group is considered clinically important. Assuming a type I error protection of 0.05 and a power of 0.80, 24 patients in each group are required for a comparison within the group. Considering the difference between the two treatment groups at a 5 % significance level with an estimated 20 % dropout rate, 30 patients in each group are required in this study.

### Statistical analysis

All primary and secondary endpoints will be analyzed on an intent-to-treat basis. Analyses will be performed with the use of SPSS 18.0 software. The Student-t test will be used to analyze the demographic data in the two groups. The incidence of the CRBD and the side effects between the groups are analyzed by Chi-square test, whereas the severity of the CRBD (mild, moderate, and severe) will be analyzed by Fisher’s exact test. The VAS scale will be analyzed by the Mann–Whitney test. Postoperative sulfentanil requirement will be analyzed by *Z* test, and the duration of postoperative sulfentanil requirement and the number of patients requiring sulfentanil for postoperative pain will be analyzed with Fisher’s exact test. A *P* value < 0.05 is considered significant.

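### The severity half of the primary outcome is assigned Fisher's exact test on three of four ordered grades, which ignores the ordering and, read literally, compares only patients who developed CRBD

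*Protocol article*

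**What the plan says.** The Primary outcome section of the protocol article states: "The primary outcome is the incidence and severity of CRBD". It then defines four levels in increasing order. The lowest is the absence of CRBD ("no CRBD indicates that there are no complaints of CRBD at all"), followed by mild, moderate and severe.

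The Statistical analysis section splits this outcome into two tests. For incidence: "The incidence of the CRBD and the side effects between the groups are analyzed by Chi-square test". For severity: "the severity of the CRBD (mild, moderate, and severe) will be analyzed by" Fisher's exact test. The lowest level is not among the categories listed for the severity test.

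The same section promises: "All primary and secondary endpoints will be analyzed on an intent-to-treat basis". It also gives a rank test to another ordered outcome: "The VAS scale will be analyzed by the Mann–Whitney test".

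The Sample size calculation section concerns incidence only: "A difference of 30 % in the incidence of CRBD values between the DPNB group and the TRAM group is considered clinically important". No effect size or power is given for severity.

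**The concern.** There are two separate problems.

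- **Ordering.** Fisher's exact test on a table with more than two columns treats the grades as unordered labels. A shift from severe to mild counts no differently from a shift the other way. This holds whichever patients enter the table.
- **Population.** If the table has only the three listed grades as columns, only patients who developed CRBD can enter it. Having CRBD happens after randomisation, and the treatment is meant to change it. The two groups compared are then no longer the randomised groups, and the intent-to-treat statement is not met for this half of the primary outcome.

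The stake is a primary result that can mislead. A treatment that prevents mild cases and leaves the others unchanged produces a worse grade mix among those still affected, although no patient is worse off. In the opposite case, a real benefit across the scale leaves few affected patients in the table, and the test has little chance of detecting anything.

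**Working it through.** **The plan's own figures.** The dropout step reproduces: 24 / (1 − 0.20) = 30 per arm. The 24 itself cannot be checked, because no control rate is stated. Both numbers relate to incidence, so there is no planned severity power to reproduce.

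**How many patients would enter a three-grade table.** The Background gives an incidence of 47 to 90%. The Discussion reports that tramadol halves it, which gives 23.5 to 45% in the tramadol (TRAM) arm. Taking the upper end and reading the 30% difference as absolute, the dorsal penile nerve block (DPNB) arm has 45 − 30 = 15%. With 24 evaluable per arm, that is 24 × 0.45 = 10.8 and 24 × 0.15 = 3.6, or about 11 and 4 affected patients.

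**Power.** The article gives no grade mix, so every mix below is an assumption. Rows 1 and 2 set the mixes directly. Rows 3 to 5 use 50/35/15% mild/moderate/severe among affected TRAM patients and a proportional-odds shift that gives a 30-point fall. For row 4 the odds ratio is (0.60/0.40) / (0.30/0.70) = 3.5. Each cell is the simulated rejection rate at P < 0.05, shown for 24 / 30 per arm.

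| None/mild/moderate/severe, TRAM to DPNB (%) | 2×3 Fisher, affected only | Mann–Whitney, four grades, all patients |
|---|---|---|
| 1. 55/20/15/10 to 85/10/4/1 | 2% / 4% | 68% / 78% |
| 2. 40/25/20/15 to 70/17/9/4 | 6% / 7% | 60% / 70% |
| 3. TRAM incidence 45% | 1.5% / 3% | 67% / 74% |
| 4. TRAM incidence 60% | 4.5% / 5% | 60% / 70% |
| 5. TRAM incidence 90% | 30% / 40% | 88% / 95% |

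Leaving aside row 5, and with repeat runs differing by a few points, restricted Fisher is at about 2–7% and the four-grade Mann–Whitney at about 62–75%.

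**Other readings of the same sentence.**

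- A 2×4 Fisher test that includes patients without CRBD has about 48–59% power (45% in row 4 at 24 per arm).
- Fisher tests grade by grade on all patients mean three tests. Each has about 1–22% power for TRAM incidence of 47 to 75%. A move from moderate to mild also counts as an increase in mild CRBD.

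**What the plan already captures.** In the same kind of scenario the planned chi-square test on incidence has about 61–71% power. Most of the Mann–Whitney power is therefore incidence signal.

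**Direction.** Suppose DPNB abolishes mild CRBD and nothing else: TRAM 40/30/21/9%, DPNB 70/0/21/9%. Among affected patients the mix goes from 30/60, 21/60, 9/60 = 50/35/15% to 0/30, 21/30, 9/30 = 0/70/30%. Restricted Fisher rejects in about 55% of trials at 24 per arm and 75% at 30, with DPNB appearing more severe. The four-grade Mann–Whitney rejects in only 29% at 24 per arm.

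**One illustrative table** (30 per arm; mild/moderate/severe). TRAM is 14/3/1 and DPNB is 0/3/1.

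- Moderate or worse among affected: TRAM 4/18 = 22%, DPNB 4/4 = 100%. Restricted Fisher P = 0.0096.
- Four grades, all patients: Mann–Whitney P = 0.0017 in favour of DPNB.
- Incidence: 18/30 against 4/30. Uncorrected chi-square = 60 × (18×26 − 12×4)² / (30×30×22×38) = 14.07, P about 0.0002 in favour of DPNB.

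**The case against.** The strongest reply is that the exclusion is inferred. The bracketed list may only name the grades of discomfort in a condensed article. The scale includes the no-CRBD level and the analysis is declared intent-to-treat, so a table that keeps everyone would fit both statements. A reader might infer that the plan definitely discards unaffected patients and so has almost no power for severity. The text does not support that as fact: a 2×4 table would have roughly half to three-fifths power. What stands is that three grades are listed, the fourth is not, and incidence is tested separately. The literal reading is therefore the restricted one, and at the least the test is ambiguous.

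A second reply is that setting 4% against 78% compares two different questions. This is correct. The rank test on all patients gains mainly from incidence, which the chi-square test already covers. A reader might infer that the trial as a whole would usually miss a real benefit, and that is not shown.

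A third reply is that the adverse-direction example is extreme: it has no mild cases at all on DPNB, and the incidence result printed beside it would strongly favour DPNB. That is also fair. It shows a risk of misreading one primary component, not that the trial would reach the wrong overall conclusion.

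None of these replies answers the loss of ordering, which holds under every reading.

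**Conclusion.** The concern holds in this form: the severity test ignores the ordering of the scale under any reading and, read literally, is conditional on a post-randomisation outcome, which conflicts with the intent-to-treat statement.

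The loss of power depends on the reading. It is large under the restricted and grade-by-grade readings and moderate for a 2×4 table. The figures rest on assumed grade mixes, an absolute 30-point fall in incidence, and 24 to 30 evaluable patients per arm. Near 90% TRAM incidence the restricted test reaches 30–40%, so very low power is not universal, although the article's own figures point to 45% or less. The possible reversal of direction depends on the block acting mainly on mild cases, and on readers taking the severity result apart from the incidence result.

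Because severity is named as part of the primary outcome and the sentence allows several different analyses, it should be settled before any unblinded analysis.

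**What to change.** Replace the severity clause in the Statistical analysis section with one that specifies:

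- severity as a four-level ordered outcome (none, mild, moderate, severe) in all randomised patients;
- either one pre-stated assessment time or the worst grade over 0 to 6 h, since the Outcome measures section lists several assessments;
- a tie-corrected Mann–Whitney test or a proportional-odds model;
- an effect estimate with a 95% CI, such as the probability of a better grade or the common odds ratio;
- the grade mix among affected patients as description only, without a test.

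State also which of incidence and severity is the primary test. The Trial status section says the study is ongoing, so the change should be dated and made before unblinding.

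The cost is small: a short change of wording, with data already collected and a rank test already planned for pain scores. There are limits. The ordinal test overlaps with the incidence test, and it does not isolate whether CRBD that does occur is milder. A proportional-odds fit may rest on very few severe cases. The worst grade over 0 to 6 h would be a summary that the article does not yet define.

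### Duration of sufentanil requirement is a time measurement but is assigned to Fisher's exact test with no categories defined, so its length and order are ignored

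*Protocol article*

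**What the plan says.** Secondary outcomes in the protocol article lists three separate sufentanil outcomes (the drug name is spelled in two ways):

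- "Number of patients requiring postoperative sulfentanil", a yes/no outcome per patient;
- "Postoperative sufentanil requirement", an amount;
- "Duration of postoperative sulfentanil requirement", a time.

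Statistical analysis then assigns the tests. The amount goes to a Z test ("Postoperative sulfentanil requirement will be analyzed by" is all that introduces it). The other two share one test: "the duration of postoperative sulfentanil requirement and the number of patients requiring sulfentanil for postoperative pain will be analyzed with" Fisher's exact test. Neither section gives a threshold, interval or grouping that would turn duration into categories. A rank test is already in the plan, for pain only: "The VAS scale will be analyzed by the" Mann–Whitney test.

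**The concern.** Fisher's exact test compares how counts fall into categories. It suits the number of patients who need sufentanil. A duration has magnitude and order, and the test uses neither. Because duration is listed separately from the count, it is presumably meant to add information: among patients who need the drug, for how long. If the stated test cannot see length, that outcome either yields no information or returns the count result under a second name.

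The practical risk runs two ways. A non-significant P value could be reported as no difference in duration when the test could not have detected one. A significant P value could be reported as a difference in duration when it reflects only how many patients needed the drug.

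**Working it through.** **Inputs.** Sample size calculation requires 24 evaluable patients per group and allows 20 % dropout: 24 / (1 − 0.20) = 30 per group, which reproduces the stated figure. The article gives no figure for any sufentanil outcome, so the data sets below are constructed to show how the test behaves. All have 30 patients per arm.

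**The test on a 2 × k table.** With N = 60 patients, n₁ = 30 in the first arm, column totals c_j and first-arm counts a_j, each table has probability

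∏ C(c_j, a_j) / C(N, n₁).

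P is the sum over all tables no more probable than the one observed.

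**Case 1: all durations differ.** Every c_j = 1 and every C(1, a_j) = 1, so every table has the same probability, 1 / C(60, 30). All tables enter the sum and P = 1 whatever the data. With the arms completely separated, Fisher P = 1.0 and Mann-Whitney P = 3 × 10⁻¹¹.

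**Case 2: non-users scored 0, positive durations all different.** With m zeros in total and x of them in the first arm, the table probability is C(m, x) / C(60, 30), so

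P = Σ C(m, y) · C(60 − m, 30 − y) / C(60, 30), over all y with C(m, y) ≤ C(m, x).

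No duration appears in this expression. With equal arms, C(m, y) and the 2 × 2 table probability both peak at m/2 and fall away symmetrically. They rank the tables identically, and P equals the Fisher P for the count.

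- Zeros 15 v 15, positive durations completely separated: C(30, 15) is the largest term, so P = 1.0. Multiplying one arm's durations by 10 leaves it at 1.0. Mann-Whitney gives 0.077 overall and 3 × 10⁻⁶ among users.
- Zeros 20 v 10: the formula gives P = 0.0194, the same as Fisher's test on the 2 × 2 count. A permutation version (4,000 permutations) gave 0.0165 with durations separated and 0.019 without, which is simulation error around the same value.

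**Case 3: durations tied on a grid of 0, 1, 2, 4 and 6 h.** Numbers of patients at these times are 15, 9, 4, 1, 1 in one arm and 8, 4, 6, 6, 6 in the other. Fisher P = 0.021. With the hour labels scrambled, the permutation estimate is 0.0195, the same within simulation error. The formula shows why: reordering the columns does not change the product. Mann-Whitney, which uses the order, gives 0.003.

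**Contrast: duration dichotomised.** On the same grid data, 2 h or more is 4 + 1 + 1 = 6 of 30 against 6 + 6 + 6 = 18 of 30, and Fisher P = 0.003. The test does respond once a cut-off exists, but the article states none.

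**The case against.** The strongest defence is that the authors meant grouped durations. Outcome measures schedules assessments at 0, 1, 2, 4 and 6 h after arrival in the PACU. If duration were recorded on that grid or split at a threshold, Fisher's test would be valid and would respond to the distribution. An article may also leave the definition of groups to a fuller document.

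Part of this stands. It would be too strong to say that Fisher's test can never respond to duration: P = 1 needs all values distinct, and the exact repetition of the count needs all positive values distinct. But the article does not say that duration is recorded on the visit grid or grouped. Even on the grid the test ignores order (Case 3), and a cut-off chosen after seeing the data would be a new problem. The pairing of a time with this test is stated, so it is not a detail left out.

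A reader might also infer that the Z test for the amount is faulty because many patients may need no drug. The documents do not support that. They give neither the form of the Z test nor the share of non-users nor the spread of doses. In simulations with assumed log-normal doses, 30 per arm, taking it as a Z test of means, its type I error was 0.041 to 0.059. Its power against Mann-Whitney went either way:

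- 0.24 v 0.55 with 50 % v 20 % non-users, the same doses among users and log-SD 1.0;
- 0.51 v 0.23 with 50 % non-users in both arms, doubled doses and log-SD 0.5.

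All that can be said of the amount is that its Z test is not defined.

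**Conclusion.** The duration analysis is wrong as written and should be corrected. The conclusion rests on reading the sentence literally, with ungrouped times, as nothing in the article supplies categories. P = 1 when all durations differ. It equals the count result when non-users are 0, positive durations differ and the arms are equal. It is blind to order when durations are tied. The first two results are exact and need no assumption about the drug's use; the grid figures (about 0.02 against 0.003) illustrate one constructed data set.

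The reach is limited to one secondary endpoint. The primary comparison of CRBD and the sample size do not depend on it, and Fisher's exact test remains right for the number of patients requiring sufentanil.

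**What to change.** Change the sentence in Statistical analysis so that:

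1. Duration of sufentanil requirement is compared by the Mann-Whitney test, in all randomised patients, with non-users scored 0. This agrees with the stated intent-to-treat basis.
2. Duration among users is described alongside, as median and interquartile range by arm.
3. Fisher's exact test is kept only for the number of patients requiring sufentanil.

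The cost is one sentence, with no added data or patients. There is a small downside. With many zeros the overall rank test partly repeats the count endpoint and has less power for a difference confined to users (0.077 overall against 3 × 10⁻⁶ among users in the 15 v 15 example). The description among users makes such a difference visible. It should stay descriptive, because users are a group defined after randomisation.

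A Hodges-Lehmann difference is not a useful companion here. If, as an assumption, 50 % of one arm and 20 % of the other are users with the same distribution of durations, a pairwise difference is negative with probability 0.5 × 0.2 + 0.5 × 0.2 × 0.5 = 0.15 and zero with probability 0.5 × 0.8 = 0.40. The median difference is then exactly 0, and could stand beside a significant P value.
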